## Abstract

**Background:**

Substance misuse in those with severe mental health problems is common and associated with poor engagement in treatment and treatment outcomes. Up to 44% of those admitted into psychiatric inpatient facilities have coexisting substance-misuse problems. However, this is not routinely addressed as part of their treatment plan. A mental health admission may present a window of opportunity for inpatients to reevaluate the impact of their substance use. This study will aim to evaluate the effectiveness of a targeted brief motivational intervention in improving engagement in treatment and to assess how feasible and acceptable this intervention is to inpatients and staff as a routine intervention.

**Methods/Design:**

This randomized controlled trial will use concealed randomization; blind, independent assessment of outcome at 3 months; characterization of refusers and dropouts; and be analyzed according to the intention-to-treat principle. After baseline assessments, eligible participants will be randomized either to the Brief Integrated Motivational Intervention plus Treatment As Usual, or Treatment as Usual alone. Eligible participants will be those who are new admissions; >18 years; ICD-10 diagnosis of -schizophrenia or related disorder, bipolar affective disorder, recurrent depressive disorder, and DSM-IV diagnosis of substance abuse or dependence over the last 3 months. The primary outcome is engagement in treatment for substance misuse, and secondary outcomes include readiness to change substance misuse together with a cost-effectiveness analysis. Qualitative interviews with staff and participants will assess the acceptability of the intervention.

**Discussion:**

This pilot randomized trial will provide the first robust evidence base for inpatient care of people with severe mental health problems and co-morbid substance misuse and provide the groundwork for confirmatory trials to evaluate a potentially feasible, cost-effective, and easy-to-implement treatment option that may be readily integrated into standard inpatient and community-based care.

**Trial registration:**

ISRCTN43548483 Date of ISRCTN assignation: 4/17/2014.

## Background

### Substance misuse in mental health-admission units

It is now well recognized that substance misuse in those with severe mental health problems is common [1–4], associated with poor engagement in treatment and treatment outcomes [5–7] and low motivation to change drug and alcohol use [8–10]. However, poor treatment engagement is a barrier for change and good treatment outcomes [6, 10–12]. In addition, substance misuse among this population is also associated with increased psychiatric hospital admissions and is found to affect inpatient stays negatively [13]. In the UK, 22% to 44% of those admitted into psychiatric inpatient facilities for mental health problems have been found also to have coexisting alcohol or drug problems [13]. Policy guidance has pointed to the need to train staff to improve routine assessment and treatment of substance misuse as part of the clinical-management strategy of a psychiatric admission [13]. Nonetheless, this has continued to be highlighted as a significant gap in service provision, and outcomes for this group remain poor [14, 15].

As acute symptoms of mental ill health decline, this can be characterized as a time of contemplation and a window of increased awareness and insight into the factors that contributed to becoming mentally unwell and or being admitted into hospital [16, 17]. However, such increased insight may result in increased emotional distress, and research has shown that after discharge, some individuals may “seal over” the experience, in an attempt to reduce emotional distress [18]. That is, they may deny or minimize recent mental health symptoms or experiences and precipitating factors, and as a result, lose awareness of the triggers for becoming unwell [18].

Sealing over the experience of relapse was found to predict low engagement with mental health services 6 months after discharge for psychiatric inpatients [18]. However, engagement in treatment is found to be a key in improving treatment outcomes [10, 19]. Hence, we propose that a targeted brief motivational intervention could use this “window of opportunity” to increase the focus on the role drug and alcohol use may have played in the exacerbation of mental health symptoms and actively link participants with substance-misuse treatment routinely integrated within community mental health teams. Hence a mental health admission may well represent a window of opportunity for individuals who misuse substances to be offered treatment to help them reevaluate their drug/alcohol use and become aware of the negative impact of it on their mental health [13, 14, 16].

Inpatient policy guidance recommends that staff be trained in simple approaches to improve motivation and encourage change in substance use [13]. A recent Cochrane review [20] indicated mixed findings in trials of the effectiveness of long-term psychological interventions with psychosis and substance misuse, potentially because of variations in methodology and samples. However, it points to the need to evaluate brief interventions, such as motivational interviewing, to enable service providers to identify a cost-effective and easy-to-implement component that may be quickly integrated into standard care. Brief motivational interventions have demonstrated good results across the range of substances, often equivalent to longer-term interventions, across a range of populations [21–25]. Motivational interventions seek to change views about alcohol/drug use or drug/drinking behavior. This would be seen as an initial step in promoting long-term changes in behavior.

The evidence base regarding the use of motivational-based interventions with this client group is encouraging [10, 26–29]. However, the evidence suggests that brief interventions be provided within the context of a comprehensive package of ongoing integrated treatment. Thus the aim of this trial is to target drug and alcohol misuse among inpatients with severe mental health problems to determine whether offering a Brief Integrated Motivational Intervention (MI) to inpatients will lead to greater engagement in substance-misuse treatment and motivation to change substance misuse in community services after discharge.

### Hypotheses

The primary hypothesis to be evaluated is whether engagement in treatment for substance misuse can be significantly improved by the MI provided in the context of treatment as usual (TAU). The secondary hypotheses are that those receiving the MI will show greater readiness to change substance-use behavior than those receiving treatment as usual and that the MI + TAU will be more cost-effective than the TAU.

## Method/Design

The trial is funded by the National Institute for Health Research-Research for Patient Benefit and has received ethical approval from the West Midlands–The Black Country National Research Ethics Committee (REC reference: 12/WM/0369). It is a single (rater) blind, intention-to-treat analysis, prospective randomized trial to assess the feasibility and impact of a brief motivational intervention for drug and alcohol misuse in mental health admission units. The trial uses concealed randomization; blind, independent assessment of outcome at 3 months; characterization of refusers and dropouts; and analysis by intention to treat. Participants consented and then randomized on a 1:1 basis, to one of two experimental conditions: MI in the context of Treatment As Usual or TAU. Participants being recruited are adults aged 18 years or older with schizophrenia, schizoaffective or delusional disorders, bipolar affective disorders or recurrent depressive disorder, users of community mental health services; new admissions to six mental health inpatient units in the West Midlands within the acute phase of severe mental health problems; who are also misusing substances (alcohol and/or drugs). Participants are recruited from six inpatient units, including 11 acute wards and three Psychiatric Intensive Care Units (PICUs), which offer a total of 202 beds.

Recruitment to the trial began in April 2013 and is ongoing until July 2014. Follow-up assessments began in May 2013 and will be completed by September 2014.

### The intervention

The MI is offered in the context of TAU. The MI seeks to encourage participants to engage in talking about their substance use and its impact on their mental health, the fundamental first step in the process of promoting a readiness and willingness to change problematic drug/alcohol use. The initial aim is twofold; first, to increase awareness of the advantages and the disadvantages of continued substance misuse, and second, to build awareness of the impact of substance use on mental health.

The next stage encourages participants to contemplate change and make a change plan, thereby making change feel possible. Participants are provided with individually tailored psychoeducational material about substances and, between sessions, are also encouraged to access websites offering information about alcohol (”Down your Drink”) and drugs (”Talk to Frank”). Participants are offered a Peer Mentor after the first week of the intervention. The Peer Mentor will aim to show empathy and understanding during a difficult time for the participants, to share personal experiences, to offer an alternative outlook on problematic substance use, and to provide some support and solidarity.

The MI is based on specifically trained staff on the wards working alongside staff from the specialist COMPASS Programme team (a specialist “dual diagnosis” Trust-wide service) [30]. Their aim is building good collaborative relationships with participants working toward a joint goal of “keeping participants from returning to hospital”. The MI takes place over a 2-week period for four to six sessions for 15 to 30 minutes on each occasion. At the final session of the 2-week intervention, the booster session is arranged for a month.

The booster session is provided by a member of the specialist COMPASS Programme Team and attended by the participant’s Care Co-ordinator. It will seek to help consolidate motivation and transfer the skills from the MI to the community and to link participants actively with substance-misuse treatment routinely integrated within community mental health teams.

The structure of the MI attempts to map itself onto the stage of recovery in acute psychosis in a targeted manner. It targets the initial window of contemplation during the admission and then is timed to coincide with just before “sealing over” and disengagement [16, 18] are predicted to occur. The MI is delivered jointly by a staff member on the unit and a member of the specialist COMPASS Programme team [30], according to a therapy manual designed for this purpose. Staff are trained and supervised in the delivery of the MI by three of the Investigators. The standard to which staff deliver the MI is regularly monitored and assessed for fidelity and adherence.

### Treatment as usual

Treatment as usual will be documented. It is mostly provided by nursing and medical staff on the mental health admission units in line with inpatient trust policies, regularly monitored by the UK Care Quality Commission. It will primarily consist of assessment and monitoring mental state, provision of medication, and stabilization of the mental state.

### Inclusion and exclusion criteria

Eligible participants are adults aged 18 or older with severe mental health problems, who are service users of community mental health services and have been admitted to mental health inpatient units within the acute phase of severe mental health problems and who are also misusing substances (alcohol and/or drugs). They will have an ICD-10 diagnosis of schizophrenia, schizoaffective or delusional disorders (F20,22,23,25,28,29); bipolar affective disorders (F31); recurrent depressive disorder without psychotic symptoms (F33.2) (32), and be identified as misusing alcohol and/or drugs over the past month, in addition to a minimum score of 3 (abuse/dependent use based on DSM-IV diagnostic criteria for substance-related disorders) on the Clinicians Alcohol/Drugs Use rating scale over the past 3 months [31]. They also must be assessed by the Responsible Clinical Officer as having capacity to consent, and have a Care Co-ordinator in a Community Mental Heath Team. Participants who have already been entered in the trial but are re-admitted to the inpatient unit are not screened again but continue to be treated as trial participants and monitored as per protocol.

### Recruitment and randomization

Eligible participants are identified by Research Associates in conjunction with Clinical Studies Officers (CSOs) from the Mental Health Research Network, who review care records. The Research Associates complete a screening measure with Care Co-ordinators to confirm eligibility for the trial. The Research Associates then visit eligible participants within 2 weeks of admission, once the acute symptoms have been assessed as eased and the inpatient is deemed able to provide informed consent. Eligible participants are invited to take part and asked to provide informed consent.

Once informed consent to participate in the study has been obtained, the researchers administer a battery of assessments, and on completion, participants are randomly allocated either to the MI group (in the context of TAU) or the TAU group (the control group). At the end of the baseline assessment session, the researchers schedule a meeting with the participant for 2 weeks’ time, to complete the posttreatment assessments. Just before the 3-month data-collection point, the researchers contact the Care Co-ordinator to schedule a meeting for the completion of the 3-month follow-up assessment battery.

The trial uses independent central randomization by using a concealed process via Email. Both researchers are blind to participant treatment group allocation until all baseline, posttreatment, and 3-month follow-up quantitative assessments have been completed. Treatment allocation is available to the researchers once the 3-month data-collection point (primary outcome) has been completed. Participants in the MI group then complete the qualitative interview.

Data also are collected regarding the total number of participants admitted to the inpatient unit, the number who use substances, and the number who are eligible and consent to participate in the study.

Given the pragmatic design of the trial and the nature of inpatient units, it is possible that some leakage of MI components into TAU may occur through participants or staff. Participants may inadvertently discuss or share information about the MI, or inpatient staff trained to use the intervention may provide parts of it to those participants in the TAU arm. Any contamination bias will be limited by steps taken by the trial team. A number of methods will be used to reduce potential leakage. Participants will be informed of the nature of the study during the consenting process and asked not to share any information about the treatment they receive. An important component of the training sessions for Inpatient staff and Peer Mentors in the intervention arm will involve education and awareness about the importance of blinding and ensuring that only those allocated to the MI receive the elements of the intervention. This is also to be discussed during supervision sessions.

### Measures

#### Primary outcome

Primary outcome will be engagement with substance-misuse treatment while inpatients and with community treatment services at 3-month follow-up, as reported by Care Co-ordinators/primary clinician, by using the Substance Abuse Treatment scale [8, 31]. Engagement is assessed by using the Substance Abuse Treatment Scale (SATS), a widely used and standardized measure that uses an eight-stage hierarchic motivational model of engagement in substance-misuse treatment to assess the stage of recovery from substance misuse.

Care Coordinators are asked to categorize the level of engagement in substance-misuse treatment on an 8-point scale: the categories are pre-engagement, engagement, early persuasion, late persuasion, early active treatment, late active treatment, relapse prevention, and in remission or recovery. It has demonstrated high validity, reliability, and test-retest reliability [8, 31]. The reporting timeframe is adapted to the previous 3 months. An objective assessment of engagement in addressing substance misuse will also be carried out by reviewing the clinical notes of participants to assess whether any discussion of substance use has occurred, as evidenced in the clinical notes of participants from both the MI and TAU groups.

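### The primary SATS rating comes from a clinician planned to attend an MI session, so the claim of blind, independent outcome assessment does not cover the primary endpoint

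*Protocol article*

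**What the plan says.** **Blinding claimed.** Under Method/Design: "It is a single (rater) blind, intention-to-treat analysis, prospective randomized trial", with "blind, independent assessment of outcome at 3 months". The Methods paragraph of the Abstract makes the same claim of blind, independent assessment.

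**Who is blind.** Recruitment and randomization applies blinding to the two researchers, until the 3-month quantitative assessments are complete. It names nobody else.

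**Who rates the primary outcome.** Under Primary outcome, engagement is "as reported by Care Co-ordinators/primary clinician, by using the Substance Abuse Treatment scale". The next paragraph is more specific: "Care Coordinators are asked to categorize the level of engagement in substance-misuse treatment on an 8-point scale". On the period rated: "The reporting timeframe is adapted to the previous 3 months".

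**What the rater does in the MI arm.** Under The intervention, a COMPASS Programme Team member provides the booster and it is "attended by the participant’s Care Co-ordinator". On its timing: "At the final session of the 2-week intervention, the booster session is arranged for a month". One of its aims is to connect the participant with substance-misuse treatment in the community team.

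**How the rating is used.** Planned analyses makes SATS at follow-up the response variable of the principal analysis, with baseline SATS as a covariate.

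**The concern.** A rater-blind trial with independent assessment should have its primary outcome scored by someone who does not know the allocation and has no part in the treatment. Here the blind people gather the data, while the judgement that becomes the data point is made by a clinician whom the plan places in an MI session. TAU has no matching session.

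SATS asks the rater to place the participant in one of eight ordered categories of engagement. A Care Co-ordinator who attended a session intended to promote that engagement may rate it higher than one who did not, with the participant's behaviour unchanged. A difference between arms could then combine a treatment effect with rater expectation, yet be reported as blind-assessed. The Clinicians Alcohol/Drugs Use rating scales, completed by primary clinicians, may be affected in the same way.

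**Working it through.** **Step 1. The statements side by side.**

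| Question | What the article states | Section |
|---|---|---|
| What is promised? | Rater-blind design; blind, independent 3-month assessment | Abstract; Method/Design |
| Who is blind? | The two researchers | Recruitment and randomization |
| Who picks the SATS category? | Care Co-ordinator (or primary clinician) | Primary outcome |
| Who attends the MI booster? | The participant's Care Co-ordinator | The intervention |
| Who is taught about blinding? | Inpatient staff and Peer Mentors; Care Co-ordinators not listed | Recruitment and randomization |

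The first row cannot hold for SATS if the third and fourth do.

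**Step 2. Timing.** The booster comes about a month after a 2-week intervention, so roughly 2 + 4 = 6 weeks after MI begins. The rating is at 3 months and looks back 3 months. The booster therefore precedes the rating and lies within the rated period.

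**Step 3. Does anything in the article repair this?**
- Baseline adjustment does not. Baseline assessments precede randomization, so knowledge of allocation can affect only the follow-up score.
- The clinical-notes review covers both arms and is the protocol's own cross-check. But it asks only whether substance use was discussed, is not said to be blind, and is not the principal response variable.
- No blind SATS rater and no check on blinding is described.

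**Step 4. Illustration of sensitivity.** From Sample size: 34 per group, difference 1 point, power 90%, two-sided α 0.05. The SD is not given, so it must be solved for.
- Normal approximation: SD = √(34/2) × 1 / (1.960 + 1.282) = 4.123 / 3.242 ≈ 1.27.
- Noncentral t with 66 degrees of freedom: SD ≈ 1.25.

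The stated 68 participants are consistent with an SD of 1.25 to 1.27. This does not confirm the figure independently, because the SD was derived from it.

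With SD 1.25, the standard error of the difference is 1.25 × √(2/34) ≈ 0.303. Suppose there is no true effect and MI ratings are shifted by b stages. The noncentrality is b/0.303, and the two-sided 5% t-test rejects as follows:

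| Assumed shift b | b/SE | Rejection rate |
|---|---|---|
| 0 | 0 | 5% |
| 0.25 | 0.82 | 12.8% |
| 0.5 | 1.65 | 36.9% |

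Because the SD is uncertain, for b = 0.5 the rate is about 53% at SD 1.0, 27% at SD 1.5 and 17% at SD 2.0.

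This is an unadjusted two-sample comparison. The planned model adjusts for baseline SATS, so these rates are not those of the planned test.

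**The case against.** The strongest case on the other side accepts the contradiction but disputes how far it reaches. Most of that stands.

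- **Attending is not delivering.** COMPASS staff provide the booster. A reader might infer that the rater is a therapist in the trial; the article supports only that the rater takes part in a session.
- **Unblinding is planned, not universal.** A Care Co-ordinator may miss the booster, and the text allows a primary clinician to report instead. So the rater will usually, not always, know the allocation. No blinding is stated for either role.
- **How open SATS is to judgement is not shown.** The article calls it standardized, valid and reliable, and its scoring anchors are not printed. Reliability does not make an unblinded rating blind, but the size of any bias cannot be read from the document.
- **Spill-over to self-report.** It is tempting to add that the participant-completed measures are compromised because "Just before the 3-month data-collection point, the researchers contact the Care Co-ordinator to schedule a meeting". The article describes a scheduling contact only and says the researchers remain blind. That inference is not supported.
- **Using SOCRATES or MAP as a blind check.** These are gathered by blind researchers, but from participants who know whether they received MI. Requiring them to agree with SATS would not restore blinding.
- **Replacing the primary rater.** A researcher rating from records with MI and booster entries removed would strip evidence of engagement from one arm only. It would also no longer match the clinician-rated baseline covariate, and it would mix raters in a trial whose follow-up began in May 2013.
- **Pilot status.** The trial is groundwork for confirmatory work. That tempers the consequences but does not make the blinding statement correct.

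**Conclusion.** The concern holds for the blinding claim as it applies to the primary endpoint. The article promises blind, independent assessment, yet assigns the SATS rating to a clinician who, in the MI arm, is planned to attend an MI session before rating. Nothing in the document reconciles the two. The CAUS/CDUS ratings may be affected likewise.

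This rests on two readings: that the Care Co-ordinator is normally the rater, as the more specific sentence says, and that boosters normally take place as planned.

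A reader might infer from the rejection rates that the SATS result will be biased by a known amount. The documents do not support that, since they give neither the SD nor the size or direction of any rating shift. The figures of about 13% and 37% show only that shifts well below the 1-point target could matter. What is established is narrower: a SATS difference may include rater expectation and cannot be presented as a blind-assessed effect.

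**What to change.** 1. In the Abstract and Method/Design, limit the claim of blind assessment to the researchers and the measures they administer.
2. Under Primary outcome, describe SATS as rated by a clinician not blind to allocation, and note the same possibility for CAUS/CDUS.
3. State in advance that a SATS difference may include rater expectation and will not be reported as a blind-assessed effect.
4. Keep the Care Co-ordinator SATS as the primary outcome.
5. For participants not yet followed up, have the still-blind researchers record their own SATS stage from the 3-month participant interview, plus a guess at allocation. Report both beside the primary result as a sensitivity check.

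Items 1 to 4 cost only wording. Item 5 adds two short entries to the 3-month form, completed by staff already in place. Its drawback is that the researcher's rating will be less informed than the clinician's and will cover only a subset.

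### The supplementary notes-based check of engagement is met by receiving the MI itself, so an arm difference on it could not be read as engagement with substance-misuse treatment

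*Protocol article*

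**What the plan says.** Under Primary outcome, the protocol article defines engagement through the SATS as reported by the Care Co-ordinator or primary clinician, for the inpatient period and for community services at 3 months. It then adds a second measure: "An objective assessment of engagement in addressing substance misuse will also be carried out". The method is "reviewing the clinical notes of participants to assess whether any discussion of substance use has occurred", and it applies to both arms: "as evidenced in the clinical notes of participants from both the MI and TAU groups". The article states no other condition for this item.

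The intervention section describes the treatment in much the same terms: "The MI seeks to encourage participants to engage in talking about their substance use and its impact on their mental health". On dose it says "The MI takes place over a 2-week period for four to six sessions for 15 to 30 minutes on each occasion", and on delivery "The MI is delivered jointly by a staff member on the unit and a member of the specialist COMPASS Programme team". A booster follows at about a month: "The booster session is provided by a member of the specialist COMPASS Programme Team and attended by the" participant's Care Co-ordinator. Under Treatment as usual, the listed elements are mental-state assessment and monitoring, medication and stabilization. No planned discussion of substance use is listed.

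**The concern.** The item has the lowest possible threshold, and the allocated treatment crosses it. An MI participant who attends one recorded session and then has nothing further to do with substance-misuse treatment scores the same as one who takes up treatment in the community. A TAU participant has no comparable scheduled route to a positive score.

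The interpretation is what is at stake. A measure labelled objective, set beside a clinician rating of the same construct, is likely to be read as supporting that rating. The Care Co-ordinator who rates SATS also attends the MI booster, so independent support would be worth having. As worded, the item could show a clear arm difference that says only that the MI was delivered and written down.

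**Working it through.** The plan attaches no figure to this item, so there is none to reproduce. The sample size of 68 belongs to SATS; only its 34 per group is used below.

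**Step 1: the criterion against the treatment.**

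| Question | Notes item | MI | TAU as listed |
|---|---|---|---|
| What counts or happens | any recorded discussion of substance use | discussion of substance use | monitoring, medication, stabilization |
| How often | once is enough | 4 to 6 sessions plus a booster | none scheduled |
| Who could record it | clinical notes | ward staff co-deliver; Care Co-ordinator at the booster | ward staff |
| Exclusion of MI entries | none stated | – | – |

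One recorded session satisfies the criterion. That sessions are recorded in the clinical notes is an inference from who delivers them; the article does not state it.

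**Step 2: what delivery alone could produce.** Let q be the share of participants in either arm whose notes record discussion for reasons unrelated to the MI, and d the share of MI participants with at least one MI session in the notes. Suppose the MI changes nothing else and the two are independent. Then

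- TAU rate = q
- MI rate = 1 − (1 − q)(1 − d)

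Both q and d are assumptions.

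*Single-table illustration.* Take 17/34 = 50% in TAU and the same background of 17 in MI. If 14 of the remaining 17 MI participants have a session noted (14/17 = 82%), MI has 17 + 14 = 31 of 34 positive. The difference is (31 − 17)/34 = 41 points, Fisher exact p = 0.00037. If all 17 have a session noted, it is 34/34 against 17/34, p = 1.0 × 10⁻⁶.

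*Range.* With d = 0.85 and 34 per arm, the chance of a two-sided 5% significant difference is given first by the normal approximation, Φ[(Δ − 1.96·se₀)/se₁]. Here Δ is the difference in rates, and se₀ and se₁ are its standard errors with pooled and separate variances. The last column gives the exact value for Fisher's test, the sum of the binomial probabilities of all tables with p ≤ 0.05.

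| q (TAU rate) | MI rate | Normal approximation | Exact, Fisher |
|---|---|---|---|
| 0.40 | 1 − 0.60 × 0.15 = 0.910 | 0.998 | 0.996 |
| 0.50 | 1 − 0.50 × 0.15 = 0.925 | 0.985 | 0.975 |
| 0.60 | 1 − 0.40 × 0.15 = 0.940 | 0.93 | 0.91 |
| 0.80 | 1 − 0.20 × 0.15 = 0.970 | 0.60 | 0.43 |
| 0.90 | 1 − 0.10 × 0.15 = 0.985 | 0.32 | 0.08 |

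At low to moderate background documentation, delivery alone would almost always give a significant difference. At high background the difference shrinks, and the normal approximation overstates the chance of detecting it. At q = 1 the arms are equal and the item carries no information.

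**The case against.** Several points on the other side stand and limit the finding.

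- *The item supports no planned conclusion.* The principal analysis is SATS at follow-up adjusted for baseline, and the sample size rests on SATS. No test or decision rule is attached to the notes item. A reader might infer that the primary result is compromised, or that this item is meant to validate SATS or is the only safeguard against its rater. The article says none of this. It also collects service use with the Client Service Receipt Inventory, though it does not say that this isolates substance-misuse services.
- *Talking may itself be engagement.* The primary outcome includes the inpatient period, the SATS has early engagement and persuasion stages, and the article treats talking about use as a first step. That is fair. But when the talking is the allocated treatment, a difference between arms cannot separate engagement from allocation.
- *Detail may sit in the full protocol.* Handling of MI entries could be specified there. The criterion itself is stated in the article, however, and that criterion is what is at issue.

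Two further inferences are tempting and not supported. One is that TAU would be at ceiling because recruiting staff are those "who review care records". Finding evidence of use in records is not the same as a recorded discussion, and the Abstract's premise that substance misuse is not routinely addressed points the other way. The other is that reading the notes breaks the blind. The article does not say who reviews them or when, and it releases allocation to the researchers once the 3-month assessments are complete, so this is a risk and not a demonstrated breach.

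**Conclusion.** The concern holds for the supplementary item only. As worded, delivery of the MI can make the item positive, so a between-arm difference would not be evidence of engagement with substance-misuse treatment, nor independent corroboration of SATS.

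The size cannot be fixed from the article. It rests on two unstated quantities: how often MI sessions are written in the clinical notes, and how often substance use is discussed and recorded anyway. Under the assumed rates above, the spurious difference runs from about 51 points (91% against 40%) to 8.5 points (98.5% against 90%). The conclusion also assumes that MI entries are counted, since nothing in the article excludes them. The item should be changed, but the trial's main inference does not depend on it.

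**What to change.** Redefine the item as documented referral to, attendance at, or an agreed plan for substance-misuse treatment other than the trial's own MI, peer-mentor and booster contacts. Use the same window, randomization to 3 months, in both arms, so that the inpatient period stays in.

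A note that merely records an MI, peer-mentor or booster session does not count. A referral or plan for other treatment that arises from such a session does count: the booster exists to produce these links, and discarding them would bias the item against the MI.

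Extract the notes after that participant's 3-month assessments are complete, which removes the blinding risk for those assessments. Report any-discussion entries separately, as a measure of delivery in the MI arm and of leakage or background practice in the TAU arm.

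The cost is a revised extraction form applied to notes that are reviewed anyway, and a somewhat lower event rate on this item.
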